### 12.2. *Supply of Study Product*

Bayer will be providing regorafenib for the study and the regional co-ordinating centre will arrange for the delivery of the investigational product to sites. Imatinib will be supplied according to usual hospital practice.

### 12.3. *Drug Accountability*

The Pharmacy Department at participating institutions will maintain a record of drugs dispensed for each patient and subsequent returns. The Pharmacy will also maintain a record of drug receipt and drug destruction as appropriate.

## 13. STATISTICAL CONSIDERATIONS

### 13.1. *Sample Size*

This is a non-comparative randomized phase II design to investigate the efficacy/activity of an alternating regimen of 21-25 days of imatinib followed by a 3-7-day gap for washout followed by 21 of regorafenib and a 7-day gap for washout. The control group will be a regimen of continuous imatinib in a 56 day cycle. In order to demonstrate clinical activity, the response rate at 9 months is deemed to be an appropriate endpoint. Study and resource constraints limit the sample size in the alternating regimen to 38 patients and as such the measured activity will be primarily descriptive. The anticipated sample size of the study will be 60 evaluable patients in an unequal randomisation ratio

# ALT GIST

average approximately 2:1 randomisation (22 in the control and 38 in the alternating group). Based on a 95% one-sided confidence interval (Mehta and Cain, *JCO* 1984; 2 (6):676-681), for different levels of the true underlying response rate, the table below gives the minimum number of responses required to be observed in the alternating group. Accrual may continue beyond 60 patients, but any increase would be modest.

|                     | True response rate (%) |      |      |      |
|---------------------|------------------------|------|------|------|
|                     | 30                     | 40   | 50   | 60   |
| Number of responses | ≥ 7                    | ≥ 10 | ≥ 13 | ≥ 17 |

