### Statistical considerations

This is a non-comparative randomized phase II design of 60 evaluable patients allocated 2:1 (38 in the alternating group and 22 in the control), The primary outcome is the objective tumour response rate by 9 months. Based on accrual of 38 evaluable patients in the alternating group, the table below, based on the charts of Mehta and Cain, give the minimum number of responses needed to be observed to be consistent with different response rate.

|                     | True response rate (%) |      |      |      |
|---------------------|------------------------|------|------|------|
|                     | 30                     | 40   | 50   | 60   |
| Number of responses | ≥ 7                    | ≥ 10 | ≥ 13 | ≥ 17 |

These limits are based on 95% lower confidence intervals for the respective response rates.

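### Two of the four response counts for the alternating arm (13 and 17 of 38) do not match the stated one-sided 95% level, and the wording hides that the counts only fail to exclude each rate

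*Protocol*

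**What the plan says.** The table appears twice in the protocol with the same entries: at least 7, 10, 13 and 17 responses for true rates of 30, 40, 50 and 60%. The text around it differs.

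- **Synopsis, Statistical considerations.** "Based on accrual of 38 evaluable patients in the alternating group", the charts of a cited paper are said to "give the minimum number of responses needed to be observed to be consistent with different response rate". Below the table it adds: "These limits are based on 95% lower confidence intervals for the respective response rates".
- **Section 13.1, Sample Size.** The basis is given as "Based on a 95% one-sided confidence interval", "for different levels of the true underlying response rate", and "the table below gives the minimum number of responses required to be observed in the alternating group". The planned split is "22 in the control and 38 in the alternating group". Earlier in the section: "In order to demonstrate clinical activity, the response rate at 9 months is deemed to be an appropriate endpoint".

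Section 13.1 also says that study and resource constraints set the figure of 38 and that the activity result is mainly descriptive. Section 13.2 assesses activity by the response proportion with a 95% confidence interval and does not say whether that interval is one-sided or two-sided. No uninteresting rate, target rate, power or go/no-go rule is attached to the table.

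**The concern.** There are two separate problems.

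First, the row can be checked against the level that section 13.1 states, and two of its four entries fail. A count printed as consistent with a 50% or 60% rate is, at that level, evidence against it.

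Second, the words around the table point in different directions. The synopsis idea of consistency describes a non-exclusion table, in which a low count is acceptable until the upper confidence limit falls below the rate. Calling the limits *lower*, and in section 13.1 calling the counts *required*, suggests a table of counts that establish the rate. Those are very different numbers.

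The aim is to judge whether the regimen is active enough to warrant further evaluation, and this table is the only place where the protocol links observed counts to true rates. Someone working from section 13.1 alone could set 17 of 38 (44.7%) beside the 60% column and take it as support for a 60% rate.

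**Working it through.** **Inputs.** n = 38 (synopsis and section 13.1); one tail of 0.05 (section 13.1, one-sided 95%); p = 0.30, 0.40, 0.50, 0.60; printed counts 7, 10, 13, 17.

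**Rule.** With X ~ Binomial(38, p), a count r does not exclude p at one-sided 95% if P(X ≤ r | p) > 0.05. This is the same as saying that the exact (Clopper-Pearson) one-sided 95% upper limit, the 0.95 quantile of Beta(r + 1, 38 − r), reaches p. It also gives the same number as the largest r with P(X ≥ r | p) ≥ 0.95, so reading the table as a lower bound on the responses expected at each true rate does not change the answer. The protocol does not write out a formula; this is the exact form of what it describes.

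**Check of the printed row.**

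| True rate | Printed | Tail probabilities | Exact minimum |
|---|---|---|---|
| 30% | 7 | P(X ≤ 6) = 0.0359; P(X ≤ 7) = 0.0795 | 7 |
| 40% | 10 | P(X ≤ 9) = 0.0268; P(X ≤ 10) = 0.0572 | 10 |
| 50% | 13 | P(X ≤ 13) = 0.0365; P(X ≤ 14) = 0.0717 | 14 |
| 60% | 17 | P(X ≤ 17) = 0.0409; P(X ≤ 18) = 0.0784 | 18 |

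The first two entries are reproduced and the last two are each one too low. In confidence limits:

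| Count | Observed rate | One-sided 95% upper limit | One-sided 95% lower limit |
|---|---|---|---|
| 7/38 | 18.4% | 31.8% | 9.0% |
| 10/38 | 26.3% | 40.5% | 15.0% |
| 13/38 | 34.2% | 48.8% (below 50%) | 21.6% |
| 17/38 | 44.7% | 59.3% (below 60%) | 30.9% |

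For 14/38 and 18/38 the upper limits are 51.5% and 61.8%, which reach 50% and 60%.

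**Could another method at one-sided 95% explain it?** No method tried does. Wilson, Agresti-Coull, Jeffreys, mid-P, a uniform-prior Bayesian limit, Anscombe arcsine and continuity-corrected Wald all give 7, 11, 14, 18. Plain Wald gives 8, 11, 15, 18 and plain arcsine 8, 11, 14, 18. Every one needs at least 14 for 50% and exactly 18 for 60%.

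**Could another level explain it?** At one-sided 97.5% (two-sided 95%):

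- Exact: 6, 9, 13, 17.
- Wilson, Agresti-Coull, uniform prior: 6, 10, 13, 17.
- Plain Wald and plain arcsine: 7, 10, 14, 17.
- Mid-P, Jeffreys, Anscombe arcsine and continuity-corrected Wald: 7, 10, 13, 17, which is the printed row.

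The exact binomial also gives the printed row for a one-sided tail between about 0.0360 and 0.0365, which is not a conventional level.

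**Could another n explain it?** With the exact method, no n from 33 to 42 gives the row at either level. The nearest are n = 37 at one-sided 95% (7, 10, 14, 17) and n = 36 (6, 10, 13, 17).

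**What showing a rate would take (reference only).** The smallest r with P(X ≥ r | p) ≤ 0.05, so that the one-sided 95% lower limit is above p, is 17 for 30% (0.0388), 21 for 40% (0.0409), 25 for 50% (0.0365) and 29 for 60% (0.0268).

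**The case against.** The strongest reply is that the label may be wrong and the counts right. The counts are said to come from published charts, not from a stated exact calculation, and several respectable approximate methods give the whole row at one-sided 97.5%. Section 13.2 speaks of a 95% interval without a side. If that interval is two-sided and exact, 13/38 gives 19.6% to 51.4% and 17/38 gives 28.6% to 61.7%, which include 50% and 60%. This stands. A reader might infer that the counts must be wrong, or that no recognised level yields the row, and neither inference is supported. What is shown is that the row and the stated level disagree.

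Next, it can be said that *lower* is only loose wording for the low end of the responses expected at each true rate, and that the synopsis already speaks of consistency. This partly stands. The calculation is not reversed, and the synopsis verb is fair. But the sentence under the synopsis table refers to confidence intervals for the response rates, and the lower limits of the printed counts are nowhere near the column headings. Section 13.1 drops the idea of consistency altogether.

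Finally, nothing operational depends on the table. This stands, and it limits the severity. A reader might take the table as the success rule for the primary endpoint, or take the phrase about demonstrating activity as a claim for these counts. The protocol supports neither: that phrase justifies the choice of endpoint, the next sentence of the section calls the result mainly descriptive, and section 13.2 rests the analysis on the proportion and its interval.

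**Conclusion.** The point holds at moderate severity. At the stated one-sided 95% level with n = 38, the smallest counts that do not exclude 30, 40, 50 and 60% are 7, 10, 14 and 18. The printed 13 and 17 exclude 50% and 60% at that level, with tail probabilities of 0.036 and 0.041. Each error is one response. The description needs correction as well, because none of the four counts shows that its rate is reached.

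The conclusion rests on 38 evaluable patients, on the one-sided 95% level in section 13.1, and on reading the table as a non-exclusion table, which is the only reading near the printed figures. The cited charts were not available, so a difference in chart reading or method there cannot be ruled out. The sample size, trial conduct and primary analysis are unaffected. It would go too far to say that the design lacks a needed success criterion and must adopt 17, 21, 25 and 29: the trial is declared non-comparative and descriptive, and those figures only mark how far the printed counts are from establishing a rate.

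**What to change.** Make the same change in the synopsis and in section 13.1.

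1. **Reconcile row and level.** Either print at least 7, 10, 14 and 18 at one-sided 95% by the exact binomial, or keep 7, 10, 13 and 17 and state the level and method that produce them (for example one-sided 97.5%, mid-P or Jeffreys).
2. **Describe the counts correctly.** Call them the smallest counts out of 38 whose upper confidence limit reaches the stated true rate, that is, counts consistent with the rate. Replace the reference to lower confidence intervals in the synopsis and the word *required* in section 13.1. Wording the rule as a confidence limit also keeps it usable if the evaluable number is not 38, since section 13.1 allows modest extra accrual.
3. **State the limit of the table.** Add that these counts do not show that the rate is reached, giving the one-sided 95% lower limits of 9.0, 15.0, 21.6 and 30.9%. These belong to 7, 10, 13 and 17; if the row becomes 7, 10, 14 and 18, the last two are 23.8% and 33.3%. The counts 17, 21, 25 and 29 may be given for reference, not as a criterion.

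The cost is one table and a few sentences in two places, with no more patients and no change of design or analysis. If the counts are the part that changes, two entries become slightly more demanding.

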## **14.2. Independent Safety and Data Monitoring Committee**

The AGITG Independent Data, Safety and Monitoring Committee (IDSMC) will closely monitor the trial for safety and toxicity. Apart from the interim analysis examining dose intensity in 13.3 no formal interim analysis of efficacy is planned but the IDSMC may review outcome data (PFS and OS) if it is felt appropriate. The IDSMC will pay particular attention to the rate of participant drop-out from trial (especially in the experimental arm) for reasons of toxicity or participant/clinician preference.

The IDSMC will provide independent assessment of patient safety and trial progress, making recommendations to the TMC about the continuation of the trial based on data made available by the trial statistician. Additionally, the IDSMC will review all SUSARS in a timely manner after appropriate authorities have been notified as detailed in section 10.

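### The printed minimum response counts hold only for 38 Arm B patients, but 2:1 of 60 gives about 40 and accrual may pass 60, with no rule to rescale the counts

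*Protocol*

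**What the plan says.** Section 13.1 sets the size of Arm B by resources: "Study and resource constraints limit the sample size in the alternating regimen to 38 patients". It then says "The anticipated sample size of the study will be 60 evaluable patients in an unequal randomisation ratio", and describes the split as "average approximately 2:1 randomisation (22 in the control and 38 in the alternating group"). The synopsis, under Statistical considerations, drops the qualifier and gives "60 evaluable patients allocated 2:1 (38 in the alternating group and 22 in the control"). Section 4 (Design) also states 2:1 without qualification.

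Both places print the same benchmark: at least 7, 10, 13 and 17 responses for true rates of 30, 40, 50 and 60%. Section 13.1 introduces it with the words "the table below gives the minimum number of responses required to be observed in the alternating group" and ties it to a one-sided 95% confidence interval read from published charts. The synopsis ties it to n: "Based on accrual of 38 evaluable patients in the alternating group".

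Just before the table, section 13.1 adds: "Accrual may continue beyond 60 patients, but any increase would be modest". It gives no number for modest, no reason for an extension, and no adjustment of the counts.

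Section 13.2 makes the primary result the proportion responding by 9 months, with a 95% confidence interval.

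**The concern.** A minimum count is a statement about one sample size. Seventeen responses mean something different among 38 patients than among 40 or 44. The protocol fixes the counts for 38 but makes two other statements under which Arm B would not be 38: an unqualified 2:1 ratio applied to 60, and permission to accrue past 60. It also says resources limit Arm B to 38 and then, in the same section, lets the trial grow.

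The counts are worded as required, and they are the only numerical yardstick offered for the stated aim of judging whether the regimen has sufficient activity. If the final Arm B is larger than 38 and the result is read against the printed row, the report could call the data consistent with a response rate that the data exclude.

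**Working it through.** **Inputs.** Arm B n = 38, total 60, and counts 7/10/13/17 for 30/40/50/60% (13.1 and synopsis). One-sided 95% (13.1). Ratio 2:1 (synopsis and section 4) and 38:22 (synopsis and 13.1). The protocol does not say how the interval is calculated, so an exact binomial limit is taken as the main reading and others are tried.

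**Rule.** A count k is compatible with a true rate p if the upper confidence limit for k out of n reaches p. For the exact one-sided 95% limit, the minimum is the smallest k with P(X ≤ k | n, p) > 0.05.

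**Reproducing the table at n = 38.**
- Exact one-sided 95%: 7/10/14/18. In the 50% column P(X ≤ 13) = 0.0365 and P(X ≤ 14) = 0.0717, so the minimum is 14. In the 60% column P(X ≤ 17) = 0.0409 and P(X ≤ 18) = 0.0784, so the minimum is 18. Equivalently, the upper limit is 48.8% for 13/38 and 59.3% for 17/38.
- Exact two-sided 95%: 6/9/13/17.
- Two-sided 95% by mid-p or Jeffreys: 7/10/13/17, which matches all four columns.

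The table is therefore built on 38. An exact one-sided 95% limit matches only its 30% and 40% columns.

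**Allocation.** 60 × 2/3 = 40, whereas 38/22 = 1.73. Strict 2:1 gives 40:20.

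**Counts at a larger Arm B.** The sizes 42 and 44 are assumptions (63 × 2/3 and 66 × 2/3), because the protocol gives no maximum. The table shows the exact one-sided counts, and the Jeffreys two-sided counts because they match the printed table at 38.

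| Arm B n | Exact one-sided 95% | Change from n = 38 | Jeffreys two-sided 95% | Change from n = 38 |
|---|---|---|---|---|
| 38 | 7/10/14/18 | – | 7/10/13/17 | – |
| 40 | 7/11/15/19 | 0/1/1/1 | 7/11/14/18 | 0/1/1/1 |
| 42 | 8/12/16/20 | 1/2/2/2 | 8/11/15/19 | 1/1/2/2 |
| 44 | 8/12/17/21 | 1/2/3/3 | 8/12/16/20 | 1/2/3/3 |

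The change due to n alone is the same under both methods at 40 (0 to 1) and at 44 (1 to 3).

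**Seventeen responses against the 60% row.**

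| Arm B n | Observed | Exact upper limit, one-sided 95% | Exact upper limit, two-sided 95% |
|---|---|---|---|
| 38 | 44.7% | 59.3% | 61.7% |
| 40 | 42.5% | 56.7% | 59.1% |
| 44 | 38.6% | 52.1% | 54.5% |

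At 38 the answer depends on the limit chosen. At 40 neither limit reaches 60%.

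**Chance of meeting a fixed count when the true rate is 20 points lower than its column.** P(X ≥ 17 | true 40%) is 0.33 at n = 38, 0.43 at 40 and 0.63 at 44. P(X ≥ 13 | true 30%) is 0.34, 0.42 and 0.58.

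**The case against.** The strongest reply is that nothing turns on the table. Section 13.1 calls the trial non-comparative and its measure of activity primarily descriptive. The estimate and interval in section 13.2 are computed at whatever n is reached, and no go/no-go rule is attached to the counts. The synopsis labels the table as being for 38, so applying it to 44 is a misuse. Section 13.1 also says approximately 2:1 and writes out 38 and 22, so 40 is not a concealed sample size. All of this stands, and it limits the size of the point. It does not remove it: the counts are worded as required, the same section permits a larger n, and no instruction says to recompute them.

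A reader might infer more than the documents support:

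- **Inflated type I error.** That would need a test repeated as patients accrue. The protocol contains none, and section 14.2 says "no formal interim analysis of efficacy is planned but the IDSMC may review outcome data (PFS and OS) if it is felt appropriate". No inflation is claimed.
- **Accrual steered by the response count.** The trial is open label and sites see their own patients' scans. But the protocol does not say who decides on extra accrual or that pooled Arm B responses are tabulated. The review allowed in 14.2 is by the IDSMC and names PFS and OS, and section 11.2 leaves final classification to retrospective central review.
- **The whole gap at 44 is due to over-accrual.** Setting the printed 17 against an exact 21 gives four responses, but one of them is already present at 38 (17 against 18). Only three come from n.
- **The split should be 40:20.** The documents do not show which of the two figures is the intended one, and 40 would conflict with the stated limit of 38.

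**Conclusion.** The point holds as an inconsistency in a stated benchmark. The counts 7/10/13/17 apply to 38 evaluable Arm B patients. The unqualified 2:1 ratio and the over-accrual sentence both lead to a larger Arm B, and the counts are then too lenient by 0 to 1 response at 40 and 1 to 3 at 44. A count of 17 falls short of the 60% row at 40 on either exact limit.

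Separately from n, the 50% and 60% columns are one response low at 38 if the stated one-sided 95% interval is an exact one.

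The consequence is limited to interpretation against the printed table; the primary proportion and its interval are unaffected. The figures for 42 and 44 rest on an assumed meaning of modest, and the exact calculation is a reading of a method that the protocol does not name.

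**What to change.** In section 13.1 and the synopsis:

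1. Define the benchmark as the one-sided 95% confidence limit at the actual number of evaluable Arm B patients. Replace the single row of counts with a short table for about n = 36 to 46, computed by one named method. If that method is the exact one, the 38-patient row becomes 7/10/14/18.
2. Reconcile 2:1 with 38:22 in the synopsis, section 4 and section 13.1 by stating the ratio actually used.
3. Reconcile the stated limit of 38 with the sentence that allows accrual past 60.
4. Optionally, state a maximum Arm B number and say that any extension is decided without reference to response by arm.

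While editing, name the n to be used: section 9.1 divides by evaluable patients, while section 13.2 includes all randomised patients.

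The cost is wording and one small table, with no extra patients. The downside is that the counts become slightly stricter if more than 38 are enrolled.

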## 13.2. Statistical Analysis

Analyses will include all patients who were randomised. Treatment activity will be assessed by the proportion, together with the 95% confidence interval, of patients having an objective response at or before 9 months. Similar proportions will be determined in the control group,

Time-to event endpoints of progression free and overall survival and time to treatment failure will be described using the method of Kaplan-Meier. Treatment failure is defined as the first event before 12 months of death, disease progression and unacceptable toxicity causing study treatment to cease or patient preference to cease therapy. For purposes of treatment failure, only events in the first 12 months will be considered. Patients not experiencing a treatment failure within 12 months will be censored at 12 months. While there will not be any formal comparisons between the two groups, exploratory comparative analyses may be performed. For time-to-event outcomes, these will include univariate logrank and multivariate proportional hazards comparisons. Other exploratory analyses will also be performed as appropriate.

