## Design

Prospective, randomised, open label phase II trial, stratified by participating site, previous adjuvant therapy (prior vs none), and previous imatinib for metastatic disease for less than or equal to 25 days prior to randomisation.

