## 4. DESIGN

Prospective, randomised, open label phase II trial, with randomisation 2:1 by minimisation and stratification by site, receipt of previous adjuvant therapy (prior vs none), and receipt of imatinib for metastatic disease for less than or equal to 25 days.

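### The exploratory comparison names an unstratified log-rank test and does not tie its proportional hazards model to the two binary minimisation factors: a minor, cheap improvement

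*Protocol*

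**What the plan says.** Section 4 (Design) gives the allocation scheme of this open-label study as follows: "with randomisation 2:1 by minimisation and stratification by site, receipt of previous adjuvant therapy (prior vs none), and receipt of imatinib for metastatic disease". The last factor concerns at most 25 days of prior treatment. The Design part of the synopsis lists the same three factors.

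Section 13.1 calls the trial non-comparative, plans 60 evaluable patients (38 alternating, 22 control), and says that "as such the measured activity will be primarily descriptive".

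Section 13.2 describes the time-to-event endpoints by Kaplan-Meier. On comparing the arms it says: "While there will not be any formal comparisons between the two groups, exploratory comparative analyses may be performed". For the time-to-event endpoints, these analyses are to include "univariate logrank and multivariate proportional hazards comparisons". The section does not say which covariates enter the multivariate model, does not link either analysis to the minimisation factors, and sets no significance level for the comparison.

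**The concern.** Minimisation makes the arms more alike on the chosen factors than chance would. If those factors predict outcome, the difference between arms varies less from trial to trial than the unstratified log-rank variance assumes. The test then rejects too rarely under the null and loses power. This goes beyond a detail left unwritten, because the protocol names a test and describes it as univariate, which leaves out the factors on which the trial balances.

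What is at stake is modest. This is the only comparative use of the randomised control arm for these three endpoints, and with about 60 patients precision is scarce. Leaving the model's covariates open in a small open-label trial also leaves room for a choice made after the data are seen.

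**Working it through.** **No stated figure to reproduce.** The protocol gives no significance level, power, hazard ratio (HR) or event count for this comparison. The check is therefore a simulation, with conventional settings supplied for it.

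**Inputs from the protocol.** 60 patients; 2:1 minimisation on site and two binary factors (Sections 4 and 13.1); a median progression-free survival on imatinib of about two years (Section 1), used only to set the time scale.

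**Assumed inputs.** 15 sites with no site effect; a biased coin of about 0.8 towards balance; exponential times; censoring uniform over 18 to 54 months; factor prevalences of 25% and 50%, or 15% and 30%; the same prognostic HR for each factor (1, 1.5, 2 or 3); treatment HR 1 for size and 0.5 for power; two-sided 5% tests.

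**Model.** Monthly hazard = (ln 2 / 24) × (factor HR)^(number of factors present) × (treatment HR)^(alternating arm). The 24-month median thus applies to a control patient with neither factor.

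**Tests.** The log-rank statistic is Z = Σ(O − E) / √ΣV, summed over event times in one pool (unstratified) or within the four cells of the two factors (stratified). The third test is the treatment coefficient from a Cox model that includes the two factors.

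**Results.** 4,000 trials per scenario; Monte Carlo standard error about 0.0035 for size and 0.008 for power.

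| Factor HR | Prevalences | Size: unstratified | Size: stratified | Size: Cox | Power: unstratified | Power: stratified | Power: Cox | Stratified minus unstratified power (points) |
|---|---|---|---|---|---|---|---|---|
| 1 | 25%, 50% | 0.058 | 0.060 | 0.058 | 0.457 | 0.432 | 0.453 | −2.5 |
| 1 | 15%, 30% | 0.054 | 0.049 | 0.050 | 0.466 | 0.446 | 0.460 | −2.1 |
| 1.5 | 25%, 50% | 0.051 | 0.057 | 0.061 | 0.522 | 0.502 | 0.537 | −2.0 |
| 1.5 | 15%, 30% | 0.048 | 0.052 | 0.052 | 0.496 | 0.472 | 0.509 | −2.5 |
| 2 | 25%, 50% | 0.039 | 0.053 | 0.056 | 0.486 | 0.517 | 0.560 | +3.1 |
| 2 | 15%, 30% | 0.041 | 0.054 | 0.052 | 0.487 | 0.486 | 0.523 | −0.1 |
| 3 | 25%, 50% | 0.026 | 0.056 | 0.055 | 0.433 | 0.560 | 0.598 | +12.7 |
| 3 | 15%, 30% | 0.034 | 0.049 | 0.053 | 0.430 | 0.522 | 0.555 | +9.1 |

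The last column is taken before rounding. Three things follow.

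- Omitting the factors does not inflate the error rate. The highest unstratified sizes occur at factor HR 1, where nothing prognostic is omitted.
- The conservatism comes from the balanced allocation. With simple randomisation at factor HR 2 (prevalences 25% and 50%), the unstratified size is 0.0525, against 0.0393 with minimisation.
- The adjusted Cox model has at least the power of the stratified log-rank test in every row. Without prognostic effects it gives up less than one point against the unstratified test (0.4567 to 0.4527, and 0.4662 to 0.4600). Its size runs from 0.050 to 0.061, so part of its advantage may reflect a slightly liberal test.

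**Sensitivity to the assumptions.** A separate set had a 38:22 split, prevalences of 30% and 40%, and 6,000 trials per scenario. With factor HRs of 3 and 1.7, power rose from 47% to 55% and size from 3.7% to 5.4%. With HRs of 2 and 1.4, power was 51% against 52%. With no prognostic effect it fell from 47% to 44%. A further repeat of the minimisation runs put the unstratified size at about 0.044 for factor HR 2 and 0.026 to 0.038 for HR 3, with a gain from stratifying of about 3 and 8 to 14 points respectively.

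**Scale.** By the Schoenfeld formula, power = Φ(|ln HR| × √(D × p × (1 − p)) − 1.96), with p = 38/60 and HR 0.5. With D = 30 events, √(30 × 0.2322) = 2.64, and 2.64 × 0.693 − 1.96 = −0.13, so power is 45%. It is 56% with 40 events and 66% with 50. The comparison is weakly powered whichever test is used.

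**The case against.** The strongest reply is that the same sentence also names a multivariate proportional hazards model, which is the natural place for the factors. An unadjusted and an adjusted result side by side is an ordinary pairing, the covariate list is something an SAP commonly settles, and Section 13.2 leaves room for further exploratory analyses. This largely stands. A reader might infer that the plan disregards the allocation factors altogether. The text does not support that: only the log-rank test is described as univariate, and the model is merely not tied to the factors.

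A reader might also infer that stratifying restores a required error rate at no cost. That fails on both counts. The comparison is optional, with no significance level or decision rule to restore, and the stratified test loses 2 to 3 points of power when the factors carry no information.

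The prognostic strength is also assumed. The protocol gives no prognostic hazard ratio or prevalence for either factor. Its argument that drug exposure selects resistant clones (Section 1) makes prior adjuvant imatinib a plausible prognostic factor, but Section 5.2 excludes patients who progressed on it. Prior imatinib of at most 25 days mainly records when randomisation fell relative to starting the same drug, and Sections 9.2, 9.4 and 9.6 already move time zero for these patients. An HR of 3 per factor is therefore an upper scenario, not an expectation.

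Finally, the simulation is scaled to progression-free survival. Overall survival was not simulated, and time to treatment failure is censored at 12 months, so the sizes do not carry over directly to those endpoints.

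**Conclusion.** The point holds as a minor one. Section 13.2 names a log-rank test that leaves out the factors used for allocation and does not commit the accompanying model to them. If the two binary factors are clearly prognostic, the unstratified test is conservative: size about 0.04 at HR 2 per factor and 0.03 to 0.04 at HR 3, with about 0 to 3 and 8 to 14 points of power lost. At HR 1 to 1.5 its size is already near 5% and there is nothing to correct. These figures rest on the assumed prevalences, prognostic effects and censoring listed above.

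A reader might infer a raised false-positive risk, or a threat to the trial's conclusions. Neither follows. Omitting the factors did not inflate the error rate in any scenario, and the primary analysis is a response proportion in each arm with its confidence interval, which this does not touch.

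**What to change.** In Section 13.2, state that any exploratory time-to-event comparison will account for prior adjuvant therapy and prior imatinib for metastatic disease, as covariates in the proportional hazards model and as strata for the log-rank test, with the unadjusted result kept as supportive. If the SAP already says this, bring the protocol sentence into line with it.

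The change is one sentence and one line of code. It needs no new data, because both factors are recorded for allocation. It should be fixed before any comparison of the arms is seen. The statistical cost is about 2 to 3 points of power for the stratified log-rank test if neither factor is prognostic. Site would stay unadjusted because it has too many levels for 60 patients. The fix therefore covers two of the three minimisation factors, and the text should say so.
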